### Randomization

Participants are randomized in a 2:1 ratio to one of 2 treatment arms, with twice as many participants allocated to receive active stimulation of the pre-SMA compared to sham rTMS. This unequal allocation was chosen to maximize the number of participants receiving the active intervention and to enhance recruitment by increasing the probability of assignment to active treatment.

Randomization is stratified by study sites to ensure balanced allocation across centers. Randomization sequences are generated using Castor EDC. Each site implements block randomization using randomly permuted blocks of size 6 to maintain allocation balance within each center and minimize group size imbalances that may arise due to site-specific factors, such as varying levels of experience with rTMS.

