### Setting of the Study

This multicenter trial is carried out in specialized mental health care facilities across the Netherlands. Participants are recruited through multiple channels: outpatient clinics with extensive experience in the treatment of OCD, self-referral, and through the patient organization for Anxiety and OCD. The patient organization was also actively involved in the design of the trial, and one of their representative lived experience researchers participates in the monthly research meetings to support ongoing collaboration and alignment with patient perspectives. The 5 participating sites geographically cover the country, enabling treatment in the catchment area of the participants’ home. These 5 sites are located in Amsterdam (Amsterdam UMC/GGZ inGeest), Nijmegen (Radboudumc/ProPersona, with MRI scans at Donders Center of Cognitive Neuroimaging), Maastricht (Maastricht UMC+/Mondriaan groep, with MRI scans at Scannexus), and Eindhoven and Groningen (2 sites of neurocare clinics). Participants from Eindhoven and Groningen undergo MRI scans in either Amsterdam or Nijmegen, based on their preference. The 5 centers aim to contribute equally to patient inclusion (between 35‐60 participants per site). The following rTMS machines are used in this trial: Magstim rapid2 (Amsterdam UMC, Radboudumc, Maastricht UMC+) and Deymed XT 35 (neurocare Eindhoven and Groningen).

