### Blinding

Participants, ERP therapists, and those carrying out clinical and cognitive assessments are blinded to treatment conditions. The rTMS treatment administrators are not blinded due to the technical nature of this treatment; however, they are instructed not to disclose treatment allocation to participants, therapists, or blinded assessors.

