### Challenges of the Proposed Trial

As of January 2026, we have faced several challenges in the ongoing trial. Coordinating rTMS and ERP, often administered at different locations, has proven logistically complex, requiring careful scheduling among rTMS technicians, therapists, and participants. In Amsterdam, prior experience with the TIPICCO trial enabled the site to begin enrolling the targeted participants concurrently without delay [19]. In contrast, other sites experienced slower start-up times due to difficulties in assembling the full treatment teams, leading to delays in filling participant slots. As a result, the trial has progressed unevenly across sites, with Amsterdam compensating for these delays by enrolling a larger number of participants.

Recruitment also poses challenges, particularly at certain sites. In some cases, this is due to competition from existing intensive ERP programs or a lack of familiarity with rTMS among general practitioners and other referring clinicians. Additionally, some potential participants decline to take part due to the requirement for randomization—especially given that rTMS for OCD is already available in the private (self-paid) health care sector. The intensive treatment schedule (4 sessions per week over 5‐7 wk) is also a barrier for some people, as it can be difficult for participants to manage alongside work or other responsibilities, requiring significant flexibility from both participants and their employers.

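### One fixed block size of 6 per site at 2:1, with unblinded rTMS administrators, lets up to about 29% of assignments be deduced by someone who holds a site's full allocation history

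*Protocol article*

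**What the plan says.** The Randomization section gives the allocation in three statements. The ratio: "Participants are randomized in a 2:1 ratio to one of 2 treatment arms", with twice as many on active stimulation. The stratification: "Randomization is stratified by study sites to ensure balanced allocation across centers". The blocking: "Each site implements block randomization using randomly permuted blocks of size 6". Six is the only block size mentioned. On the source of the lists it says: "Randomization sequences are generated using Castor EDC".

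The Blinding section says: "The rTMS treatment administrators are not blinded due to the technical nature of this treatment". The safeguard it adds is that "they are instructed not to disclose treatment allocation to participants, therapists, or blinded assessors".

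The article does not say who screens participants, who triggers randomization, or whether administrators know the block size. The Results section reports 201 participants enrolled by February 2026 against a target of 250, so 49 remained.

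**The concern.** With a single block size, allocation becomes predictable towards the end of each block for anyone who has followed the sequence. Once both sham places are used, every remaining place is active. Once all four active places are used, the rest are sham. The sixth place is always determined. Because the lists are separate by site, the history needed is only that of one site. The unblinded administrators are the people there who could accumulate it.

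If such knowledge reached whoever decides when a participant is randomized, a participant could be steered, even without intent, towards a known active or known sham place. The primary ANCOVA adjusts for baseline Y-BOCS I, so steering on severity measured by that scale would largely be dealt with. Steering on traits outside the model, such as motivation for exposure work, would not. Motivation could matter here because both arms depend on engagement with intensive ERP.

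**Working it through.** The article gives no predictability figure, so there is nothing of its own to reproduce first.

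**Inputs.** Ratio 2:1, block size 6 and separate lists by site (Randomization); 5 sites with 35 to 60 participants each (Setting of the Study); 250 planned (Sample Size Calculations); 201 enrolled from April 2022 to February 2026 (Results).

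**Upper bound: full knowledge.** A block of 6 has 4 active and 2 sham places, which can be ordered in 15 ways. An assignment is certain when one arm is already used up.

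| Position | Certain in | Share |
|---|---|---|
| 1 and 2 | 0 of 15 | 0% |
| 3 | 1 of 15 | 6.7% |
| 4 | 3 of 15 | 20.0% |
| 5 | 7 of 15 | 46.7% |
| 6 | 15 of 15 | 100% |

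The total is 26/15 = 1.733 per block, and 26/90 = 28.9% of assignments. The closed form agrees: 4/(2+1) known active + 2/(4+1) known sham = 1.333 + 0.400 = 1.733.

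**Incomplete last blocks.** At 35 per site: 5 × 1.733 + 0.733 = 9.4, or 26.9%. At 50 per site: 8 × 1.733 + 0 = 13.87, or 27.7%; over five such sites, about 69 of 250. At 60 per site: 10 × 1.733 = 17.33, or 28.9%.

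**Incomplete knowledge** (block size and boundaries still known).
- Latest allocation not yet known: each row of the table moves down one position, giving (1 + 3 + 7)/90 = 11/90 = 12.2%.
- Latest two not known: (1 + 3)/90 = 4/90 = 4.4%.
- Each earlier allocation known with probability q: [(4/3)q² + (2/5)q⁴]/6. At q = 0.75 this is (0.750 + 0.127)/6 = 14.6%; at q = 0.5 it is (0.333 + 0.025)/6 = 6.0%.

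**Pace of enrolment.** 201 participants over 5 sites and about 46 months is 201/(5 × 46) = 0.87 per site per month. On average, therefore, the previous allocation may often be known before the next is made. The interval from randomization to first session is not stated, and Amsterdam enrolled more than the other sites.

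**Gain from guessing.** With full knowledge the best guess is right 74.4% of the time, against 66.7% from always guessing active.

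**Varying the block size.** Simulation of 50 participants per site, for an observer who knows the set of sizes and every earlier allocation but is not told where blocks end:

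| Sizes | Certain assignments | Best guess correct |
|---|---|---|
| 6 only | 27.9% | 74.0% |
| 3, 6 | 9.9% | 75.1% |
| 6, 9 | 5.3% | 72.8% |
| 3, 6, 9 | 3.6% | 73.4% |
| 6, 9, 12 | 2.1% | 71.6% |

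Rerunning 3, 6, 9 for fresh lists of only 10 per site gave about 3% certain, so the result does not depend on long lists. Varying the size removes certainty. It hardly changes the accuracy of an ordinary guess.

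**Remaining participants.** 250 − 201 = 49, about 10 per site. At 28.9%, about 14 of these could be deduced under full knowledge.

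**The case against.** A reader might infer that about 29% of assignments are in fact known in advance and that allocation is not concealed from the administrators. The document does not support this, for four reasons.

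- The article says that administrators are unblinded. It does not say that any one of them sees the whole site sequence, knows the block size or knows where blocks begin. The 29% needs all three.
- The remark in Challenges of the Proposed Trial about "requiring careful scheduling among rTMS technicians, therapists, and participants" concerns fitting together rTMS and ERP sessions, often at different locations. It gives technicians no role in eligibility, consent or the order of entry. The same section reports that some candidates decline because of randomization, which is no evidence that staff time entries.
- The lists come from Castor EDC. How upcoming allocations are withheld is a detail that a condensed article may leave to the full protocol, so silence on it proves nothing.
- The article reports status as of February 2026, so its publication cannot have informed the first 201 assignments.

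It is also fair that 1.333 of the 1.733 certain places per block are active, already the likelier arm, and that few participants remain. Nor does the block size by itself unblind anyone: a participant, therapist or assessor would first have to learn other people's allocations, which the Blinding section forbids.

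All of this stands, and it limits the size of the point. It does not remove it. The single block size is a stated choice, and pairing it with unblinded site staff creates predictability that a different list would avoid.

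**Conclusion.** The point holds as a minor design weakness. Up to 28.9% of assignments in complete blocks, or 27.7% at 50 per site, could be deduced by an observer who knows the block size, the boundaries and every earlier allocation at the site. Under less complete knowledge the share is about 12% (latest allocation unknown), 15% (75% of earlier ones known) or lower. Whether anyone holds that knowledge, or could act on it, is not stated. No bias in Y-BOCS points can be estimated from the document, and none is claimed here. Any harm would come through selection on traits the ANCOVA does not include. The planned sample size is not affected.

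**What to change.** 1. For participants not yet randomized, generate new site lists in Castor EDC with block sizes varying at random in multiples of 3, and do not disclose the sizes to the sites. Small sizes such as 3, 6 and 9 are preferable to sets including 12, because only about 10 participants per site remain and long blocks may not finish.
2. State in one sentence that rTMS administrators have no part in eligibility decisions or in the order or timing of randomization. If the full protocol already says so, cite it.
3. For those already enrolled, tabulate baseline characteristics by arm, separately for assignments that were determined within their block and those that were not. The subgroups are small, so a clean table would be weak reassurance only.

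**Cost.** New lists in the existing system, one sentence and one table. Balance within site loosens slightly. The largest possible departure of the active count from 2:1 within a block of size m is 2m/9, which rises from 1.33 participants at m = 6 to 2 at m = 9. A block left unfinished at the switch can add up to a further 1.33. The new lists protect only the remaining enrolment, at most about 14 assignments.

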### Intervention

Treatment consists of 4 sessions per week in which each rTMS session is immediately followed by a 90-minute ERP session. This offers the logistical benefit of catching up on a missed treatment during a treatment week. The treatment follows an adaptive design, offering a minimum of 20 sessions to all participants with a possible extension of 4 or 8 sessions for participants who continue to show improvement and/or are motivated to continue therapy (see decision rules below) for optimal treatment effect. Change in symptoms is measured weekly during the treatment by administration of the Y-BOCS-II [37] to obtain a severity score after every 4 individual sessions. After 4 weeks of combined treatment, the process of the treatment is evaluated with the patient and one of the clinicians to decide if treatment should be continued after the 5th week. The decision process on (dis)continuation always follows shared decision making and is independent of treatment allocation; in case of doubt, the case is to be discussed in the weekly indication & treatment meeting. Participants who, after clinical evaluation, feel that they can still benefit from treatment can continue. If clinicians and participants agree that treatment will not be beneficial anymore or if participants worsen during treatment, treatment is discontinued. At the end of week 6, we again monitor progress using the same criteria, allowing participants who continue to show steady (partial) response the opportunity to undergo a seventh week of treatment, amounting to a maximum of 28 sessions per participant. This design allows participants who are experiencing protracted and slowly accruing benefit from the repeated combined sessions to maximize their treatment effect; and it accounts for the slow and linear benefit of repeated rTMS sessions that has been observed in adults with OCD, who still improve at or after 20 sessions [38,39]. Additionally, it allows for participants not benefiting enough from the treatment to exit the study and prevent unnecessary burden.

### rTMS Parameters

Previous meta-analyses have shown conflicting and inconclusive results about the efficacy of different stimulation targets and protocols in OCD [40-42]. We based our choice of stimulation location, intensity, duration, and frequency on recommendations from international guidelines and following the pairwise and network meta-analysis that our group carried out prior to the start of the study [8]. Treatment thus combines low-frequency (1-Hz) rTMS over the pre-SMA with ERP, administered immediately after the rTMS session. The intensity of stimulation is set at 110% of resting motor threshold (RMT), determined in one session a week before the start of the treatment, by trained experimenters through visual observation of muscle activation in the first dorsal interosseous muscle of the right hand, in response to handheld single-pulse stimulation. RMT is defined as 2 motor responses in a series of 4 consecutive single-pulse stimulations. In the verum rTMS condition, we deliver 1500 continuous 1-Hz pulses to the pre-SMA, that is, 25 minutes of stimulation. This protocol allows us to obtain a maximum stimulation effect while conforming to internationally published safety guidelines [18].

### TMS Coil Placement and Recording of Sessions

The positioning of the TMS coil on the scalp is based on the EEG 10‐20 coordinate system. To localize the pre-SMA, the midpoint between the tragi is first identified and marked. Using this reference point, the nasion-inion distance is measured with a flexible measuring tape. From the nasion, 35% of the total nasion-inion distance is measured along the curved path of the tape, ensuring it passes through the previously marked midpoint between the tragi. The location corresponding to this 35% point (15% anterior of the vertex) is marked on the scalp as the pre-SMA target site. The coil is placed on the marker with the handle pointing in the posterior direction.

Precision of the rTMS coil positioning is recorded using neuronavigation during the 1st, 10th, and 20th sessions [43], available in all collaborating centers. The procedure of neuronavigation requires the use of a high-resolution T1-weighted MRI scan, registered to the participant’s head upon co-registering visible landmarks on the head of the participant with landmarks on the MRI scan. The use of neuronavigation software allows us to record the location of every single pulse of stimulation throughout the treatment session and for post-hoc verification of the precise stimulation location in the participant’s MRI in native space, and at group level in standard space.

This approach will allow us to post-hoc map individualized resting-state functional connectivity-based coordinates (or even multimodal MRI-based coordinates) relative to the actually stimulated coordinate in order to relate treatment success to stimulation location (distance between actual and optimal fMRI-based coordinates). This approach will serve to inform us on the added value of MRI-based individualized targeting using neuronavigation versus nonneuronavigated rTMS treatments. This is relevant for future use of MRI-based neuronavigation in daily clinical practice.

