## Methods

### Study Design

This study is a 2-arm randomized controlled trial (RCT) with an active adjuvant rTMS treatment with ERP delivered 4 times per week; the control condition involves sham rTMS combined with ERP. Treatment duration is adaptive, based on clinical improvement, and consists of a minimum of 20, and a maximum of 28 combined rTMS-ERP sessions. Participants undergo a baseline MRI scan session to analyze pre-to-posttreatment changes in brain structure and function and for prediction analyses of response and relapse. Blood sampling is performed at baseline, directly posttreatment, and at 3 months follow-up. Participants, ERP therapists, and clinical assessors remain blind to treatment conditions during treatment and follow-up. Outcome measures are assessed at baseline, posttreatment, and at 3, 6, and 12 months follow-up. A subset of these measures are assessed weekly during treatment (see outcome measures). Neuronavigation is used to record coil placement during the 1st, 10th, and 20th session.

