### Comparator

The comparison group receives 4 days per week sham-rTMS (using a sham coil) followed by 90 minutes of ERP similar to the other treatment arm. Sham-rTMS delivers pulses at an intensity that is insufficient to affect brain activity but still mimics the sensation on the scalp. As a result, it is considered a null treatment, with any clinical effects in this group attributed to ERP alone. Sham treatment is performed over the same location, that is, pre-SMA, to further ensure blinding of the participant to the treatment condition. Additionally, the other rTMS parameters, 1500 continuous 1-Hz pulses at 110% of the RMT, are identical to those used in the active (verum) condition.

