Blood sampling at baseline, directly posttreatment, and at 3-month follow-up is performed to establish markers of treatment-induced neuroplasticity and predictors of treatment response.Pre- and posttreatment MRI scans to analyze ERP and rTMS-induced effects on multiple levels in the brain, using innovative multimodal neuroimaging.Pretreatment structural and functional MRI scans to assess brain structure and network activation and connectivity to predict treatment response.

Exploratory variables:

Patient adherence to treatment protocol, as measured using the Patient Exposure and Response Prevention Adherence Scale (PEAS; [53]) and its relationship to treatment outcome. This scale is carried out by the therapists as part of usual treatment.Difference between responders and nonresponders on circadian rhythm and other sleep disorders at baseline as defined by the Holland Sleep Disorders Questionnaire (HSDQ), as a possible prognostic marker for response [54,55].The relationship of demographic and clinical variables (gender, age, age of onset, medication status), preexisting comorbidities (ie, comorbid tics, depression, anxiety, and autism), and treatment history to the treatment outcome. A simplified Dutch version of the Mini-International Neuropsychiatric Interview (MINI) for *DSM-5*-diagnoses is used to confirm OCD diagnosis and establish current comorbidity [56]. To specifically evaluate symptoms of comorbid autism spectrum disorder, the Dutch version of the Autism Spectrum Questionnaire (AQ-NL) [57] is administered.The Y-BOCS-II symptom checklist [37] is used to categorize symptom dimensions and examine treatment effects and underlying mechanisms in different OCD subgroups.Measuring the exact stimulation location as ascertained and recorded by neuronavigation on 3 separate sessions (session 1, 10, and 20) will allow us to map the variation in achieved location in relation to treatment outcome.Variation in treatment expectancy (7-item credibility and expectancy questionnaire) [58] and blinding success (1-item question “in which condition do you think you were?”) in relation to treatment outcome.

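### The coil-location recordings cannot show what neuronavigated targeting adds, because every coil is placed by scalp measurement and distance from target is only observed

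*Protocol article*

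**What the plan says.** In the section TMS Coil Placement and Recording of Sessions, the pre-SMA site is found with a tape at 35% of the nasion-inion distance. That point "is marked on the scalp as the pre-SMA target site. The coil is placed on the marker with the handle pointing in the posterior direction". No arm or subgroup is exempted. The role of neuronavigation is given there as "Precision of the rTMS coil positioning is recorded using neuronavigation during the 1st, 10th, and 20th sessions", and Study Design agrees: "Neuronavigation is used to record coil placement during the 1st, 10th, and 20th session".

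Individual fMRI-based coordinates are then to be mapped afterwards "in order to relate treatment success to stimulation location (distance between actual and optimal fMRI-based coordinates". The section concludes that this will "inform us on the added value of MRI-based individualized targeting using neuronavigation versus nonneuronavigated rTMS treatments" and calls that relevant to everyday clinical use.

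Outcome Measures lists the recordings among the exploratory variables, saying they "will allow us to map the variation in achieved location in relation to treatment outcome". Randomization describes two arms only, verum and sham, at 2:1. Under Comparator, "Sham treatment is performed over the same location", and sham is regarded as inert, so that any improvement in that arm is ascribed to ERP.

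**The concern.** Evidence on navigated versus non-navigated treatment needs people treated each way. Here everyone is treated the non-navigated way. What remains is a natural spread of distances around the scalp mark, and that spread is not randomized.

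Distance depends on where the coil lands and on where the individual map places the optimum. The second part comes from baseline functional imaging, and the article lists baseline imaging in general as a possible predictor of outcome. Site is another candidate: Randomization mentions differing rTMS experience between sites, and the ERP section describes clinicians of varying experience. All participants receive intensive ERP, and the Hypotheses expect meaningful improvement under sham, so outcomes will vary for reasons unrelated to stimulation.

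A correlation between distance and outcome could therefore arise with no targeting effect at all. If it were read as the sentence invites, it would count in favor of MRI-guided placement in routine care.

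**Working it through.** **Is there a navigated group?** Placement is by scalp mark for all, neuronavigation records only, and the randomized contrast is verum versus sham. The number treated at an individualized target is 0.

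**The plan's own sample size** (effect size 0.4, two-sided alpha 0.05, power 0.80, 2:1).
- Normal approximation: sham n = (1 + 1/2) × (1.960 + 0.842)² / 0.4² = 73.6, so 74 sham + 148 verum = 222.
- Noncentral t: 75 + 150 = 225, power 0.804. With 10% dropout, 225/0.9 = 250.

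The stated figures reproduce. They concern verum versus sham only; the article gives no figure for the location analysis.

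**How large could a spurious association be?** The inputs below are assumptions, not figures from the article: location has no effect, one unmeasured factor correlates equally with distance and outcome, the test is done in verum only, and all 150 have usable recordings.
- Spurious r = product of the two correlations; noncentrality = r × √150; false-positive rate = P(|Z| > 1.96).
- 0.2 and 0.2: r = 0.04, noncentrality 0.49, rate about 8%.
- 0.3 and 0.3: r = 0.09, noncentrality 1.10, rate about 20%.
- 0.4 and 0.4: r = 0.16, noncentrality 1.96, rate about 50%.

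**Does contrasting the arms help?** In 4,000 simulated trials per setting (150 verum, 75 sham), distance was made purely prognostic, with the same distance-outcome correlation in both arms and no stimulation effect.

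| Assumed distance-outcome correlation | Verum-only test rejects | Arm contrast rejects |
|---|---|---|
| 0.1 | 23.8% | 5.5% |
| 0.2 | 70.7% | 5.2% |
| 0.3 | 96.7% | 4.8% |

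The correlation here is the total between distance and outcome, so the 0.1 row is the one to set beside r = 0.09 above.

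**What does the contrast cost?**
- With equal residual variance and equal spread of distance in both arms, the ratio of standard errors is √[(1/150 + 1/75) × 150] = √3 = 1.73.
- Detectable correlation within verum at 80% power: Fisher z = 2.802/√147 = 0.231, r about 0.23.
- Detectable difference between arms: 2.802 × √(1/147 + 1/72) = 0.403 on the Fisher z scale, that is, r about 0.38 versus 0.

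These are best cases. Neuronavigation requires a T1 scan, and the Participants section admits people who cannot undergo MRI, so fewer than 150 and 75 may be usable.

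**The case against.** A reader might infer that the plan ignores the sham arm. The article does not support that. Neither section limits the recording or the analysis to verum, and neither specifies a model. The Dissemination Plan says all analysis plans will be preregistered on OSF, and a condensed article may leave the model for an exploratory variable to such a plan. All that can be said is that the article is silent on the use of sham.

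A reader might also infer that the trial promises a test of neuronavigation. The wording is softer: the recordings are to inform, the mapping is done afterwards, the variable is exploratory, and neuronavigated targeting appears in neither the Aim nor the Hypotheses. That limits the weight of the point. It does not remove it, because the sentence itself names the comparison and carries no caveat.

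The false-positive figures rest on assumed correlations and on a verum-only test that the article does not state. Some confounding routes, such as head size or coil operator, have no documentary support as predictors of ERP response. For site, Sample Size Calculations says center will be a covariate. These objections stand against treating the figures as estimates, but not against the fact that distance is unrandomized.

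The interaction is no complete remedy either. If anatomy or connectivity changes the response to rTMS itself, the interaction stays confounded, and it has low power. Even a clean interaction would not compare navigated with non-navigated treatment.

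**Conclusion.** The point holds for the stated inference. With no participant treated at an individualized target, the trial cannot estimate what navigated targeting adds, and no analysis plan can supply the missing group. What it can examine is whether the rTMS effect varies with distance from an MRI-defined target under scalp placement, as an exploratory and observational question.

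The distance-outcome association alone cannot distinguish accuracy from prognosis. The 8%, 20% and 50% rates illustrate how far it could mislead; they depend on the assumed correlations, a verum-only test and 150 usable recordings. The arm contrast is the better basis for inference because sham is given over the same site and regarded as inert, but its benefit is confined to prognostic confounding that is the same in both arms.

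The primary endpoint, the randomization and the sample size are unaffected.

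**What to change.** 1. Replace the sentence on added value with wording such as: *This exploratory, hypothesis-generating analysis examines whether the rTMS effect varies with distance from an MRI-defined target under scalp-based placement; it does not compare neuronavigated with nonneuronavigated treatment.*
2. In the preregistered plan, base any targeting inference on the distance-by-arm interaction for posttreatment Y-BOCS I, adjusted for baseline Y-BOCS I and center. Report the verum and sham slopes with confidence intervals beside it, and the number in each arm with usable MRI and navigation data.
3. State there that distance is not randomized, and that the interaction does not remove confounding by factors that modify the response to rTMS.

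The rewording is the essential part. The cost is text in the article and the OSF plan; the protocol's recording rule is not limited to verum, so no new data collection is implied. The statistical price is the wider interval and low power shown above, which suits a hypothesis-generating analysis but should be declared in advance.
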